### Economic evaluation

The Economic Evaluation will be presented from two perspectives: 1) a Societal Perspective, including the costs of all types of health services (direct costs) and the costs that stem from production losses (indirect costs); and 2) Health System (including only direct costs). Although NICE [87] recommends just performing economic evaluations from the Health System perspective, we will present both due to the major impact that depression has on productivity [6,88,89]. The time frame of this study will be 18 months. Therefore, we will discount both costs and effects at 3.5% following NICE recommendations [87]. All costs will be expressed in euros (€) for the reference year 2012.

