#### Cost

We will use a modified version of the Client Service Receipt Inventory (CSRI) [90] to collect information about use of health care resources, use of psychotropic drugs (antidepressants, anxiolytics and hypnotic-sedatives) and lost productivity.

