#### Unit costs

Direct health costs will be calculated by multiplying the number of health service units (consultations, hospital days, etc.) by their standard cost price. This unit cost will be retrieved from ‘Oblikue dataset’ (http://www.oblikue.com/). Cost of medication will be calculated by multiplying cost price per daily dose, multiplied by the number of prescription days recommended, as recalled by the patient. Information about medication costs will be obtained from the Spanish Pharmaceutical Vademecum (http://www.vademecum.es/). Indirect costs consist of the costs of absenteeism from paid work. Costs of work loss will be calculated by multiplying the days on sick leave by the minimum daily wage in Spain according to the human capital approach.

Intervention costs will include only the printed leaflet. However, we will also identify primary care visits related directly to the predictD-CCRT intervention.

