1. Family-oriented practice: FPs often bring a family orientation to bear in their clinical practice [102]. It has been reported that there are up to 5 levels of family-centered medical care in primary care [103]. We believe that the FP in our study are at the third level: FPs take an active interest in the feelings and concerns of the family in an empathic way. Family-oriented practice should be understood from the system theory, so that a change in any element of the family system could prevent depression in the patient. For example, a FP could help to improve the quality of life of a person who has the responsibility of caring for a relative with Alzheimer’s Disease and this may prevent depression [28]. This is feasible because in Spain members of the same family usually share the same FP. Primary care patients think it is useful to involve the family and consider the family resources and the possibility of involving other family members in coping with the risk of depression [97].

1. Social prescribing and community referral by FPs: Many social and personal problems cannot be dealt with effectively by the FP and require community resources [104]. The social dimension of the practice of primary care is the least accepted by FPs [105] and little is known about the effect on health of social prescribing and community referral by the FP. However, we will encourage FPs in the intervention group to become familiar with the community resources in their area. We will advise them on using centers. Moreover, we will advise them on using social prescribing in patients deemed appropriate with the aim of preventing depression. Primary care patients suggested participation in informal support groups to help them restructure their lives [97].

1. Management of physical problems: some physical problems are considered risk factors for depression, such as serious diseases (cancer, heart attack, stroke, …) [20,24], disabling illness (blindness, deafness, arthritis, …) [26] and/or chronic health problems (diabetes, chronic pain, …) [25]. Moreover, in our predictD studies [33,34] poor physical quality of life was an important predictor of depression, and FPs will receive this information in the patient’s reports. Therefore, appropriate management of physical problems could also help prevent depression.

4) *Offering a booklet to prevent depression*

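### The perspective labelled societal has no place for the social and community services that the intervention encourages in one arm only, so any between-arm difference in their use is costed at zero

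*Protocol article*

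**What the plan says.** Under Economic evaluation, the article plans two perspectives. The one labelled societal is "a Societal Perspective, including the costs of all types of health services (direct costs) and the costs that stem from production losses". The health-system perspective keeps the direct costs only.

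The subsections on cost and unit costs carry this scope through:

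- A modified Client Service Receipt Inventory (CSRI) is used "to collect information about use of health care resources, use of psychotropic drugs (antidepressants, anxiolytics and hypnotic-sedatives) and lost productivity".
- "Direct health costs will be calculated by multiplying the number of health service units (consultations, hospital days, etc.) by their standard cost price". Medication is priced separately.
- "Indirect costs consist of the costs of absenteeism from paid work".
- "Intervention costs will include only the printed leaflet", although primary care visits related to the intervention will also be identified.

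Under Intervention, the third component includes an item on social prescribing and community referral. It says that "we will encourage FPs in the intervention group to become familiar with the community resources in their area" and that "we will advise them on using social prescribing in patients deemed appropriate with the aim of preventing depression". The explanatory model numbers this item 3.4 and makes its activation depend on the patient's risk factors, the physician's skills and the patient's preferences. The section on the control group says that control physicians do not attend the training workshop.

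**The concern.** An incremental cost is sound only if the resources that the intervention is meant to change are counted in both arms. Here one component points patients towards services outside the health sector, and the broader perspective leaves those services out. The omission is tied to the arm: the study prompts such use among intervention physicians and not among control physicians.

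The article itself treats community-level activity as important. Under Randomized allocation, the possibility that some components are delivered at community level is part of the reason for randomizing health centers.

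At stake is what the societal cost-effectiveness and cost-utility ratios can claim. If a community service replaces a health-care contact, the contact avoided counts as a saving and its replacement costs nothing. Use that was never recorded at the follow-up interviews is also hard to recover later.

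**Working it through.** No figure in the article states the size of this gap, so there is none to reproduce. The check sets the cost scope against the intervention content and then works out how sensitive the ratio is.

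**Step 1: where would non-health social and community services be counted?**

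| Place in the article | Content stated | Such services named? |
|---|---|---|
| Economic evaluation, societal perspective | health services, production losses | no |
| Economic evaluation, health-system perspective | direct (health service) costs | no, consistent with its definition |
| Cost (modified CSRI) | health care, psychotropic drugs, lost productivity | no |
| Unit costs | health service units, medication, absenteeism, leaflet | no |
| Sensitivity analyses | health-care unit costs, discount rate, absenteeism wage, presenteeism; list left open | no |
| Quality control of the intervention | number and content of intervention visits | no (visits, not services used afterwards) |

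Component 3.4 promotes these services in the intervention arm only. Their contribution to the societal incremental cost is therefore zero by construction, whatever patients use.

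**Step 2: sensitivity of the cost-effectiveness ratio.**
Input from Sample size: cumulative incidence of 12% in the control arm and 5 points lower in the intervention arm, so the planned effect is 0.12 − 0.07 = 0.05 cases prevented per patient.

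ICER = incremental cost / incremental effect. If a net cost of *c* euros per patient (intervention minus control) is left out, the ICER moves by *c* / 0.05 = 20*c*. One euro omitted per patient is 20 euros per case prevented; ten euros is 200.

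**Step 3: an assumed range for referral alone.**
The article gives neither uptake nor price. Assume that 5% to 50% of intervention patients use extra services at a net 50 to 500 euros each:

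- Low end: 0.05 × 50 = 2.5 euros per patient; 2.5 / 0.05 = 50 euros per case prevented.
- Middle: 0.10 × 200 = 20 euros per patient; 20 / 0.05 = 400 euros per case prevented.
- High end: 0.50 × 500 = 250 euros per patient; 250 / 0.05 = 5,000 euros per case prevented.

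The spread is 100-fold, which shows how little the documents fix the size.

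**Step 4: the sign.**
Let each case of depression carry *S* euros of social-service use, so that each prevented case saves *S*. Then *c* = referral cost per patient − 0.05 × *S*, and the shift in the ICER is (referral cost / 0.05) − *S*. With an assumed referral cost of 10 euros per patient, the two parts cancel at *S* = 10 / 0.05 = 200 euros per case. Below that value the omission favors the intervention; above it, it works against the intervention. The article gives no value for *S*.

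**Step 5: cost-utility.**
The shift is *c* divided by the QALY gain. The article plans no QALY gain, so no figure is given here.

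**The case against.** The best defense is that the article states its scope openly. It says what the societal perspective contains and adds it because of depression's effect on productivity. How wide such a perspective must be is partly convention. This stands as far as it goes: nothing is concealed, and renaming would settle the labelling part. It does not answer why a resource that the intervention itself promotes is costed at zero in the broader analysis.

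Second, the CSRI is a modified version whose items are not shown, so an item on social services may exist. That is possible. But the perspective and the pricing rules are stated positively, and as written they would not bring such an item into the cost. A social worker inside the health center may fall within the counted health services; this narrows the gap to services outside the health sector.

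Third, a reader might infer that the societal ratios are biased towards the intervention. The documents do not establish this. Component 3.4 is optional for each patient, the article calls the social dimension the part of practice least accepted by family physicians, and the informal support groups it mentions may cost little. Control physicians may also refer under usual care. Fewer depressed patients could mean less social-service use, which would reverse the sign.

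Fourth, a reader might infer that no planned sensitivity analysis could address the gap. The list is explicitly open, so one could be added. None is named for these costs, and without recorded use it would have to rest on assumed quantities.

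**Conclusion.** The mismatch holds. The perspective called societal excludes a class of services that the intervention encourages in one arm, so any between-arm difference in their use is entered as zero. If referral works as intended, the intervention's cost is understated, but net direction and size cannot be determined from the article. The only firm figure is the conversion of 20 euros per case prevented for each euro of net cost omitted per patient, and it assumes that the planned 0.05 difference is achieved. The range of 50 to 5,000 euros per case rests wholly on assumed uptake and prices and ignores any offset from prevented depression.

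The point should not be stretched to both perspectives: leaving these services out of the health-system analysis follows from its definition. Cost-effectiveness and cost-utility are secondary outcomes, and the primary effectiveness analysis is untouched. It is a modest point with a cheap remedy, and it bears on what the societal ratios may be said to show.

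**What to change.** Add to the modified CSRI a short block on use of social and community services, worded identically in both arms and asked at the existing interviews. State under Economic evaluation that these services belong to the societal perspective, and under Unit costs how they are priced.

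If the block cannot be added, rename the perspective *health system plus productivity losses* and state that non-health services promoted by the intervention are excluded.

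The first option costs a few more questionnaire items and some unit-cost work, and the ratio may come out less favorable. The second costs only wording, but gives up the claim to a societal result.

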#### Cost

We will use a modified version of the Client Service Receipt Inventory (CSRI) [90] to collect information about use of health care resources, use of psychotropic drugs (antidepressants, anxiolytics and hypnotic-sedatives) and lost productivity.

#### Unit costs

Direct health costs will be calculated by multiplying the number of health service units (consultations, hospital days, etc.) by their standard cost price. This unit cost will be retrieved from ‘Oblikue dataset’ (http://www.oblikue.com/). Cost of medication will be calculated by multiplying cost price per daily dose, multiplied by the number of prescription days recommended, as recalled by the patient. Information about medication costs will be obtained from the Spanish Pharmaceutical Vademecum (http://www.vademecum.es/). Indirect costs consist of the costs of absenteeism from paid work. Costs of work loss will be calculated by multiplying the days on sick leave by the minimum daily wage in Spain according to the human capital approach.

Intervention costs will include only the printed leaflet. However, we will also identify primary care visits related directly to the predictD-CCRT intervention.

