**Figure 1 F1:**
[figure not shown]
Example of the mechanisms to reduce the likelihood of becoming depressed after the intervention to prevent the onset of depression by the family physician.

1) *Training workshop for family physicians in the intervention group*

A qualitative research study conducted prior to this RCT [97] found that FPs were resistant to informing their patients about their risk of depression, and also raised doubts about the validity of the predictD risk algorithm. FPs said they had little training on prevention of depression, and expressed uncertainties about what they should advise their patients. They were also fearful about the possible distress that could result in patients being informed of their risk for depression and commented on the lack of time for these preventive activities. Accordingly, the FPs will receive a 10–15 hour training workshop during working hours in the new intervention. This will enable them: 1) to interpret and make a specific and global evaluation of the risk for depression for each patient; 2) to transmit this information to the patient in an understandable and comprehensible way, without causing alarm; 3) to undertake active listening to patients about their beliefs, expectations and impact on information transmitted; 4) to provide tailored advice for each patient depending on his/her set of modifiable risk factors for depression; 5) to be able to integrate and personalize advice to give each patient based on his/her health history, previous doctor-patient relationship and bio-psycho-family-social circumstances; 6) to support those patients excessively worried by the information given. In the workshop we will use role-playing and video comments in groups in order to discuss and practice with FPs how to deal with different situations. The educational units, that we will use, are shown in Additional file 1: Annex 1. Previously, we will “train the trainers” to ensure that the training of the FPs will be performed to a minimum standard of quality and in standardized manner in each of the cities participating in the study.

2) *Communicating the level and risk profile of depression*

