### Explanatory model for the prevention of depression in primary care

Figure 2 shows the theoretical model that integrates the five components of the intervention to prevent depression from primary care: There are patient’s internal risk factors (sex, age, gene, personality, etc.) and external factors (threatening events) that can trigger an episode of major depression, depending on internal (coping style) and external (family and social support) resources that might be activated. Firstly, we introduce in the system “the training workshop” for FPs (*component 1*) to improve their knowledge, attitudes and skills to prevent depression with the new intervention. The FP usually has previous knowledge and a doctor-patient relationship (*component 3.1*) that generally predisposes toward a better intervention to prevent depression by both doctor and patient. We will give FPs risk information from patients, which they will use to communicate their level and profile of risk of depression (*component 2*). This is the “starting component” that will activate the rest of the components, creating a new doctor-patient interaction, whose essential element is the establishment of a basic psychotherapeutic relationship (*component 3.2*). The family-oriented practice (*component 3.3*), social prescribing and community referral (*component 3.4*), and management of physical problems (*component 3.5*) might be activated or not depending on the risk factors of depression involved in each patient, the FP’s skills, and the patient’s preferences. In all cases, FPs should provide the booklet to prevent depression (*component 4*), although the patient may or may not decide to use it. Finally, the FPs, taking into account the above components, will encourage their patients to speak about those strategies, attitudes and behavior they are already doing to prevent depression, in order to achieve their activation and empowerment (*component 5*). Thus, the patients can improve their perception of self-efficacy, which in turn promotes changes in attitudes and behaviors to prevent depression. There are also internal (sex, personality, psychosocial and preventive orientation, etc.) and external (work stress, team support, etc.) factors in the doctors that may influence their ability to conduct a successful intervention. The differences between interventions to prevent depression conducted so far in adults and the new intervention that we propose in primary care are summarized in Table 2. An example of how the intervention can lead to a reduced risk for depression is shown in Figure 1, and another example on the doctor-patient interview to prevent depression can be seen in a video (Additional file 1: Annex 3).

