### The intervention for the control group

Patients in the control group will receive “usual care”; that is, the kind of care that FPs usually provide when they are unaware of the risk profile for depression in the patients. This means explicitly that the patients and FPs in the control groups will not be informed about the risk profile at any point. FPs in the control group will not receive the training workshop.

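### Intervention cost is limited to the printed leaflet, so the 10–15 hour physician workshop that forms component 1 of the intervention is costed at zero without justification

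*Protocol article*

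**What the plan says.** Under Economic evaluation, Unit costs, the protocol article fixes the content of the intervention cost: "Intervention costs will include only the printed leaflet". The next sentence qualifies it: "However, we will also identify primary care visits related directly to the predictD-CCRT intervention".

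The Intervention section describes five components, and the first is physician training: "the FPs will receive a 10–15 hour training workshop during working hours in the new intervention". It is preceded by a further step: "Previously, we will “train the trainers” to ensure that the training of the FPs will be performed to a minimum standard of quality". The section on the explanatory model again labels the workshop component 1. The section on the control group says that "FPs in the control group will not receive the training workshop".

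Two perspectives are promised. The societal one is described as "including the costs of all types of health services (direct costs", to which production losses are added; the health-system one keeps the direct costs only. Resource use is collected with a modified Client Service Receipt Inventory (CSRI), covering health care use, psychotropic drugs and lost productivity. The Sensitivity analyses section names variations in unit costs, discount rate, absenteeism wage and presenteeism.

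**The concern.** The trial compares usual care with a package that includes training, but the economic evaluation prices the package as if the training were free. No other planned data source picks it up. The CSRI records what patients use and lose, not what physicians spend in a workshop. The qualifying sentence concerns visits, and none of the named sensitivity analyses adds training.

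Because only one arm is trained, the whole training cost belongs in the incremental cost, which the plan defines as mean cost in the intervention group minus mean cost in the control group. Leaving it out moves every result that uses this difference the same way. The bootstrap will not reveal the problem: an amount missing from every intervention patient shifts the whole distribution and leaves its spread unchanged.

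Cost-effectiveness and cost-utility are stated secondary objectives, and the Justification section says that such evidence is needed for decisions on general implementation. A health service adopting the programme would have to train its physicians.

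**Working it through.** The article states no intervention cost and no cost-effectiveness ratio, so there is no figure of the plan's own to reproduce. The check sizes what the leaflet-only rule leaves out.

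**Inputs from the protocol article**
- Intervention health centers: 35 (Randomized allocation)
- FPs per center: 2 (Family physicians)
- Workshop length: 10–15 hours per FP (Intervention, component 1)
- Intervention patients: 1643 (Sample size)
- Planned effect: 12% in controls and 5 points lower in the intervention arm, a risk difference of 0.05 (Sample size)
- Risk-communication contacts: baseline, 6 and 12 months, with a visit lasting about 10 minutes (Intervention, component 2)

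**Assumed input:** EUR 20–60 per FP hour. The article gives no hourly cost.

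**Step 1: omitted time.** Trained FPs = 35 × 2 = 70. Hours = 70 × 10 = 700 to 70 × 15 = 1050.

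**Step 2: time per intervention patient, all charged to trial patients.** 700 × 60 / 1643 = 25.6 minutes; 1050 × 60 / 1643 = 38.3 minutes. For scale, three face-to-face contacts take about 3 × 10 = 30 minutes. Low-risk patients may be told by telephone, for which no duration is given, so this comparison is approximate.

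**Step 3: hours per case prevented, without any wage assumption.** Planned cases prevented = 1643 × 0.05 = 82.15. 700 / 82.15 = 8.5 hours; 1050 / 82.15 = 12.8 hours.

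**Step 4: cost per patient = hours × rate / 1643.**
- 10 h at EUR 20: 700 × 20 / 1643 = EUR 8.52
- 10 h at EUR 60: 700 × 60 / 1643 = EUR 25.56
- 15 h at EUR 20: 1050 × 20 / 1643 = EUR 12.78
- 15 h at EUR 60: 1050 × 60 / 1643 = EUR 38.34

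**Step 5: shift in cost per case prevented = cost per patient / 0.05.** Lowest: 8.52 / 0.05 = EUR 170. Highest: 38.34 / 0.05 = EUR 767.

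**Step 6: effect of the allocation rule.** If the training serves k times as many patients as the trial arm, each figure is divided by k. With k = 10, chosen only as an illustration, the range becomes EUR 0.85–3.83 per patient and EUR 17–77 per case.

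No corresponding figure for the cost-utility ratio can be derived, because the article gives no expected QALY difference. Trainer hours and workshop materials are also unstated and are not in these figures.

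**The case against.** Several counter-arguments have weight.

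- **Only a secondary objective is touched.** Randomization, sample size, the primary outcome and the effectiveness model are unaffected, and the costing can be corrected at analysis. This stands.
- **The amounts may be modest.** The acceptability curves run from EUR 0 to 100,000, and EUR 767 is 0.77% of that span. The span is not a decision threshold, but nothing in the document shows that a conclusion would change. A reader might infer that the economic result would be invalid, or would no longer describe the intervention tested. The figures do not support that.
- **The allocation is at the upper end.** All training is charged to about 24 trial patients per FP, although physicians have larger lists and keep the skills. This stands as well. The document does not settle whether full or spread allocation should be the base case.
- **The sensitivity list is open.** It is introduced as non-exhaustive, so a training scenario is not ruled out. However, none is specified, and the base case still excludes the cost.
- **Physician contact seems to be covered.** A reader might infer that the FPs' visits are also free. That goes too far: intervention-related visits are to be identified, and consultations are priced as direct health costs. The gap is mainly the one-off training.

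The omission cannot be put down to condensation in a journal article. The rule says that the leaflet alone is counted, which is an explicit exclusion, and no reason is offered, such as treating training as a development cost.

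**Conclusion.** The point holds, as a correction that should be made to a secondary economic analysis. The direction is certain, since a positive cost borne by one arm is excluded from the incremental cost in both perspectives. The time omitted follows from the document alone: 700–1050 FP hours, or 8.5–12.8 hours per case prevented at the planned effect.

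The money value is less certain. About EUR 9–38 per patient, or EUR 170–770 per case prevented, rests on an assumed EUR 20–60 per hour, on charging all training to the 1643 intervention patients, and on the planned 5-point difference. Spreading the training lowers it; trainer time and materials raise it. The document supports a finding of bias in the intervention's favour, but not a claim that the bias would reverse a cost-effectiveness conclusion.

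**What to change.** Replace the leaflet-only rule in Unit costs. Intervention cost should comprise FP time in the workshop, trainer time including the training of trainers, workshop materials, the booklet, and intervention-related visits. Each visit should be counted once, so that one recorded both by chart review and in the CSRI is not priced twice. Apply the definition in both perspectives.

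State the allocation rule before the analysis, and report two versions: training charged wholly to trial patients, and training spread (annuitised) over the FP's list and a stated number of years. List size is already collected in the FP questionnaire. Name the source of the hourly rate, and include that rate among the unit costs varied in the sensitivity analyses.

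The cost is small: attendance hours for FPs and trainers, a wage rate and materials invoices. No patients, follow-up or power are lost. The cost-effectiveness ratio will be somewhat less favourable to the intervention.
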